#### *6.3.3.2 Secondary endpoints supporting the primary objective*

##### Time to mechanical ventilation

Analysis of the time to mechanical ventilation from the point of randomization will be undertaken by plotting Kaplan-Meier curves for each of the 2 treatment groups and by pairwise comparisons (anakinra versus standard of care) using the log rank test. Hazard ratios will be estimated using the Cox proportional hazards model and these will be presented together with 90% two-sided confidence intervals.

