### 6.3.1 General statistical issues

This design has acceptable properties in terms of the false positive potential, controlling the overall type I error at 5%, for each of the two treatment comparisons.

Secondary endpoints will be evaluated in a descriptive way. In some cases, p-value comparisons will be undertaken, but these are to be interpreted in an exploratory way.

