### 6.3.3 Analysis related to primary objective

#### *6.3.3.1 Primary endpoint*

##### Treatment success

The main outcome variable is the percentage of patients requiring mechanical ventilation at 15 days after the start of treatment. The comparison of these proportions would be done by chi-square test, with significance level 0.05 and presentation in the form of absolute risk

reduction, relative risk reduction and number needed to treat, with their respective 95% confidence intervals.

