#### 6.3.4.2 Overall mortality

Overall mortality will be analyzed at the end of the follow-up period. This endpoint will be analyzed as for time to mechanical ventilation.

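### Hazard ratios for ventilation, length of stay and mortality get 90% intervals without a stated reason, although every significance level the protocol states is 0.05 and its other effect measures use 95% (minor)

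*Protocol*

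**What the plan says.** Under the heading on time to mechanical ventilation, section 6.3.3.2 plans Kaplan-Meier curves, "pairwise comparisons (anakinra versus standard of care) using the log rank test", and Cox hazard ratios. On the hazard ratios it adds that "these will be presented together with 90% two-sided confidence intervals". It gives no significance level and no sidedness for the log-rank test.

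Three other places take over this analysis by reference: time in ICU and in hospital (also in 6.3.3.2), overall mortality (6.3.4.2) and mortality at 48 hours, 7 days, in ICU and in hospital (6.3.4.3). The wording in 6.3.4.2 is "This endpoint will be analyzed as for time to mechanical ventilation".

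Elsewhere the level is different. For ventilation at Day 15, section 6.3.3.1 says "The comparison of these proportions would be done by chi-square test, with significance level 0.05", with the absolute risk "reduction, relative risk reduction and number needed to treat, with their respective 95% confidence intervals". Section 6.3.4.1 repeats the 0.05 level and the 95% intervals for ventilation at Day 28, which is a secondary endpoint. Section 6.1 sizes the trial at a type I error of 0.05, and section 6.3.1 describes the design as "controlling the overall type I error at 5%, for each of the two treatment comparisons".

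Section 6.3.1 also says that secondary endpoints are handled descriptively and that any p-values for them are exploratory.

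**The concern.** A two-sided 90% interval belongs with a two-sided test at 0.10. The protocol names no such level and no one-sided test, and it does not explain the 90%. Two consequences follow.

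- **Mortality.** The effect on mortality is the stated secondary objective (section 3.2). A hazard ratio for death with p somewhat above 0.05 would usually be printed with an interval that excludes 1. A reader used to the 95% intervals elsewhere in the same report could take that as evidence at the 0.05 level.
- **Ventilation.** The same clinical effect would be reported as a risk difference and relative risk with 95% intervals, and as a hazard ratio with a 90% interval. The two would not be comparable in precision, and the hazard ratio would look the more precise partly because of its lower confidence level.

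**Working it through.** **1. The levels side by side**

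| Place in the protocol | Stated level | Interval |
|---|---|---|
| 6.1, sample size | 0.05 | none |
| 6.3.1, design | 5% overall | none |
| 6.3.3.1, ventilation by Day 15 | 0.05 | 95% |
| 6.3.4.1, ventilation at Day 28 (secondary) | 0.05 | 95% |
| 6.3.3.2, time to ventilation | none | 90% |
| 6.3.3.2, time in ICU and in hospital | none | 90% by reference |
| 6.3.4.2, overall mortality | none | 90% by reference |
| 6.3.4.3, mortality at 48 h, 7 days, ICU, hospital | none | 90% by reference |

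The 90% rule reaches 1 + 2 + 1 + 4 = 8 comparisons. The five mortality comparisons overlap heavily, so these are not eight independent chances of error.

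**2. What 90% corresponds to**

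A two-sided interval at level 1 − a excludes 1 when |Z| exceeds z(1 − a/2). For 90% this is 1.645, and for 95% it is 1.960. The ratio of widths on the log scale is 1.645 / 1.960 = 0.839, so the 90% interval is about 16% narrower. The two rules disagree when |Z| lies between 1.645 and 1.960, that is, when the two-sided p lies between 0.05 and 0.10. Under no effect this gap has nominal probability 0.10 − 0.05 = 0.05 per comparison.

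**3. Size on the hazard-ratio scale**

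The approximation is SE(log HR) = 2 / √events. The protocol gives no event count, so two are assumed from its own rates:

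- 18 events, from failure rates of 12% and 8% (success rates of 88% and 92% in section 6.1): 90 × 0.12 + 90 × 0.08 = 18
- 27 events, from the 15% ventilation rate in section 6.1: 180 × 0.15 = 27

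| Events | SE | 90% interval excludes 1 if HR is below | Two-sided p < 0.05 if HR is below |
|---|---|---|---|
| 18 | 0.471 | exp(−1.645 × 0.471) = 0.461 | exp(−1.960 × 0.471) = 0.397 |
| 27 | 0.385 | exp(−1.645 × 0.385) = 0.531 | exp(−1.960 × 0.385) = 0.470 |

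Example with 18 events and Z = −1.8: log HR = −1.8 × 0.471 = −0.848, so HR = 0.43 and two-sided p = 0.072. The 90% interval is 0.20 to 0.93 and the 95% interval is 0.17 to 1.08. The data are the same, but only one of the two intervals excludes 1.

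**4. Check by simulation**

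The log-rank test and the Cox Wald interval agree only approximately when events are few, so the gap was also simulated. The set-up was 90 per arm, exponential event times, 15 days of follow-up and 1,500 trials per scenario.

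| True event rates | 90% interval excludes 1 | Log-rank p < 0.05 | 90% interval excludes 1, log-rank p ≥ 0.05 | Same discordance with a 95% interval |
|---|---|---|---|---|
| 12% v 12% | 9.2% | 5.1% | 4.1% | 0% |
| 12% v 8% | 20.5% | 14.7% | 5.9% | 0% |
| 15% v 15% | 8.7% | 4.3% | 4.4% | 0% |

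In the two null scenarios the discordance (4.1% and 4.4%) is a little under the nominal 5%. This is why the statement is that such results would usually, and not always, show an interval excluding 1.

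**The case against.** The strongest reply is that these are secondary endpoints. Section 6.3.1 treats them descriptively and calls their p-values exploratory, no success, stopping or sample-size rule uses the hazard-ratio intervals, and the 90% is openly labelled. A 90% interval is a legitimate descriptive choice. All of this stands, and it is why the point is minor. It does not explain the 90%, though: Day 28 ventilation is secondary too, and section 6.3.4.1 gives it 0.05 and 95%.

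A second reply is that 90% fits a one-sided test at 0.05, since that critical value is also 1.645. The arithmetic is right, but the protocol mentions no one-sided test, and its chi-square comparisons at 0.05 with 95% intervals point to two-sided testing. Section 6.1 does link its choice of type I error to urgent need, but the value it gives there is 0.05.

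A reader might go further than the text allows in three ways.

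- *That every test is run at 0.05, so the interval contradicts its own test.* The log-rank test has no stated level. That it would be judged at 0.05 is an inference from the only level that appears anywhere.
- *That the false-positive rate of the trial is inflated.* The primary analysis in 6.3.3.1 has its own test and 95% intervals and is untouched.
- *That any p between 0.05 and 0.10 must come with an interval excluding 1.* The log-rank test and a Cox Wald interval match only approximately, particularly at 18 to 27 events.

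**Conclusion.** The inconsistency is real and minor. The protocol fixes 90% intervals for eight hazard-ratio comparisons, five of them on mortality, against a stated level of 0.05 and 95% intervals everywhere else, and gives no reason.

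The intervals are about 16% narrower on the log scale than 95% intervals. In the simulated scenarios, about 4% to 6% of trials would show an interval excluding 1 beside a log-rank p of 0.05 or more. That range assumes 12% to 15% of patients with an event under standard of care, 90 analysed per arm, 15 days of follow-up and a two-sided 0.05 reading of the log-rank test. The mismatch of levels itself needs none of these assumptions.

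What is at stake is how secondary results, mortality in particular, are read. The documents do not support a claim that the primary type I error is affected or that any decision in the trial turns on these intervals.

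**What to change.** In section 6.3.3.2, under time to mechanical ventilation, replace 90% by 95%. The cross-references carry the change to time in ICU and hospital, to 6.3.4.2 and to 6.3.4.3, so no other sentence needs editing.

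The cost is one number in the text and intervals wider by a factor of 1.960 / 1.645 = 1.19 on the log scale. Sample size, data collection and conduct do not change. If 90% was deliberate, the protocol would have to say so and give the reason, and ventilation would still be reported at two confidence levels. The change to 95% is therefore the simpler course.

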##### Change from baseline in resting SpO2 and oxygen supplementation

Change from baseline during treatment until Day 15 with measurements performed every 3 days will be summarized using descriptive statistics for each of these parameters.

##### Change from baseline in PaO2/FiO2

Change from baseline (screening) during treatment until Day 15 will be summarized using descriptive statistics.

##### Time in ICU department and in hospital

Time in ICU and time in hospital (from the point of randomization) will be analyzed at the end of the follow-up period. This endpoint will be analyzed as for time to mechanical ventilation.

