##### 3.1.2 Secondary endpoints supporting the primary objective

- Number of patients not requiring mechanical ventilation (day 28).
- Time to mechanical ventilation (days)
- Time to oxygen saturation normalization
- Stay in ICU and hospitalization (days)

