## 4 Investigational plan

### 4.1 Overall study design and plan

This is a randomized, open-label, parallel group, 2-arm multicenter study to investigate the efficacy and safety of anakinra in reducing hyper-inflammation and respiratory distress in adult patients with severe COVID-19 and CSS pneumonia.

The study consists of screening, a 2-week treatment period and a 2-week follow-up period.

The 2-week treatment period is open, and the patients will be randomized to treatment with anakinra + standard of care or standard of care alone in a 1:1 ratio.

Anakinra will be administered as 4-times daily i.v. infusions for a maximum of 15 days (Days 1 to 15), according to the patient health status and expert clinical opinion. The primary endpoint will be evaluated at Day 15.

According to hospital internal protocol, if the patient improves enough to recommend his/her discharge before the 15th day of the study, the patient will be able to continue receiving the medication at home by s.c. administration (100mg/6 hours). In any case, follow-up visits by telephone or in person will be made, depending on where the patient is, until the end of the study.

The study duration for an individual patient will not exceed 4 weeks. The end of the study is defined as last patient last follow-up visit/phone call.

Figure 1:

[figure not shown]

The study design has a total sample size of 180 patients and consists of two stages. At the end of the treatment stage, the success rates are compared between each arm: anakinra + standard of care treatment vs standard of care alone.

A data review committee composed of experts in internal medicine will be involved in the study oversight and interpretation of the study results.

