#### 4.3.2 Exclusion criteria

The presence of any of the following will exclude a patient from inclusion in the study:

- Need for oro-tracheal intubation and/or invasive mechanical ventilation at the start of the study.
- AST/ALT with values greater than 5 times normal levels.
- Neutrophils < 1.500 cell/mmc.
- Platelets < 50.000 cell/mmc.
- Sepsis or pneumonia documented by other pathogens than SARS-CoV-2.
- Existence of any life-threatening comorbidity or any other medical condition that, in the investigator's opinion, makes the patient unsuitable for inclusion.
- Inability to obtain informed consent.
- Positivity for HBV or HCV.
- Patient with active tuberculosis (It is at the discretion of the researcher to perform the tuberculin test on the patient in the screening period if it is considered a risk population and on patients with active tuberculosis manifestations).
- Pregnancy.
- Use of other previous or concomitant biological treatments. Patients in concomitant treatment with other biologicals that may interfere will be excluded: tocilizumab, canakinumab, TNFalfa inhibitors, JAKinibs
- Severe renal dysfunction (estimated glomerular filtration rate  $\leq 30$  ml / min / 1.73 m^2) or receive continuous renal replacement therapy, hemodialysis or peritoneal dialysis.
- Uncontrolled hypertension (sitting systolic blood pressure > 180 mmHg or diastolic blood pressure > 110 mmHg).
- Administration of plasma from convalescent patients who have recovered from SARS-CoV-2 infection.
- History of hypersensitivity or allergy to any component of the study drug.
- Enrollment in another concurrent intervention clinical trial, or intake of an investigational medication within three months or 5 half-lives prior to inclusion in this study, if deemed to interfere with the objectives of this study as assessed by the investigator.

- Predictable inability to cooperate with given instructions or study procedures.

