#### 4.5.3.7 Survival and hospital discharge

Data on survival and hospital discharge will be collected at Visits 5 and 6 and recorded in the CRF.

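### ICU time, listed as a stay in days, is sent to a time-to-event method that runs from randomisation and does not fit it on any reading of the text

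*Protocol*

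**What the plan says.** Section 3.1.2 lists, among the secondary endpoints supporting the primary objective, "Stay in ICU and hospitalization (days". This is a duration. No start, end or rule for patients who never enter ICU is attached to it.

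Section 6.3.3.2, under Time in ICU department and in hospital, states "Time in ICU and time in hospital (from the point of randomization) will be analyzed at the end of the follow-up period". It continues: "This endpoint will be analyzed as for time to mechanical ventilation". The method it refers to stands earlier in the same section: "Analysis of the time to mechanical ventilation from the point of randomization will be undertaken by plotting Kaplan-Meier curves", with a log-rank test and Cox hazard ratios.

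Four other places bear on the point:
- Section 4.3.2 excludes patients with "Need for oro-tracheal intubation and/or invasive mechanical ventilation at the start of the study". ICU care as such is not an exclusion.
- Section 4.1: "The study consists of screening, a 2-week treatment period and a 2-week follow-up period".
- Section 4.5.3.7: "Data on survival and hospital discharge will be collected at Visits 5 and 6 and recorded in the CRF". Table 3 has a line for time to hospital discharge but none for ICU admission or discharge.
- Section 6.3.1: "Secondary endpoints will be evaluated in a descriptive way", with any p-values treated as exploratory.

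**The concern.** A length of stay in ICU and a time from randomisation to an event are different quantities. For hospital time they nearly coincide, because the patients are inpatients at randomisation and the event is discharge. For ICU time they do not. Patients who need intubation at the start are excluded, so much of the ICU use can be expected to begin after randomisation, and some patients will never enter ICU.

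If the clock starts at randomisation and stops at ICU exit, it adds ward days to ICU days. A treatment that only postpones ICU entry would then seem to lengthen the ICU stay. If the clock is meant differently, Kaplan-Meier, log-rank and Cox methods still need an event time for each patient, and patients never admitted to ICU have none.

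This matters because Sections 2.1 and 2.2 give the preservation of ICU access as the purpose of the trial, and this is the endpoint that measures ICU use.

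**Working it through.** The protocol gives no figure for ICU stay or time to ICU entry, so there is no stated result to reproduce. The check takes each possible reading of the sentence and asks whether the prescribed method works under it. Entry times and stays below are assumptions.

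**Reading A: the bracket covers both durations, and ICU time ends at ICU exit.** This is the most natural reading. The bracket follows the joined pair, the next sentence treats them as one endpoint, and the method referred to is itself timed from randomisation.

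Measured time = time from randomisation to ICU entry + ICU stay.

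| Assumed stay, both arms | Assumed entry, control vs anakinra | Measured time | True difference in stay |
|---|---|---|---|
| 8 days | 3 vs 5 days | 3 + 8 = 11 vs 5 + 8 = 13 days | 0 |
| 10 days | 3 vs 7 days | 3 + 10 = 13 vs 7 + 10 = 17 days | 0 |

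Each day of delay adds one day. In the first row the stay is overstated by 3/8 = 37.5% and 5/8 = 62.5%. A simulation of 200,000 patients per arm, all entering ICU, used exponential entry times with mean 3 versus 6 days and an exponential stay with mean 10 days in both arms. With times cut at Day 28, the median from randomisation to ICU exit was 10.2 versus 13.2 days. The median stay counted from admission was 6.9 days in both arms.

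**Reading B: the bracket covers hospital time only.** ICU time then has no stated origin but is still sent to a method that starts at randomisation. If it is counted from ICU admission, the ward-day problem goes (10 versus 10 days in the second row). However, only admitted patients can be analysed, and treatment may influence who is admitted.

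**Reading C: ICU days accrued after randomisation.** Ward days are not counted. In the second row this gives 10 versus 10 days. In the simulation, mean ICU days accrued to Day 28 were 9.1 versus 8.6, slightly lower with later entry because less time remains before Day 28. This is a count, with zero for anyone never admitted, and not a time to an event.

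**How many patients have an ICU time.** The protocol gives no ICU admission rate. Section 6.1 gives a 15% ventilation rate in its source database, and assumed success rates of 88% and 92%. If ICU use tracks ventilation, which is an assumption:
- at 15%: 0.15 × 180 = 27 of 180 patients;
- at the assumed success rates: 0.12 × 90 + 0.08 × 90 = 10.8 + 7.2 = 18 of 180;
- at twice the 15% rate, to allow for ICU care without ventilation: 0.30 × 180 = 54 of 180.

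Between 126 and 162 of the 180 patients would then have no ICU time. In a Kaplan-Meier analysis of ICU exit they could be given an event at time zero, censored at Day 28 or left out. The first puts most of the sample at a single point. The second makes them look as if they were in ICU throughout. The third gives the post-randomisation subgroup. The protocol does not choose among these, and none gives a sound comparison of ICU stay between the randomised arms.

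**The case against.** The strongest reply is that no section says ward days count as ICU days. The bracket stands directly after the words on hospital time and may qualify only those. It may also mean that only days after randomisation are counted, which would be sensible because Section 4.3.2 does not bar a patient who is already in ICU without intubation. Section 3.1.2 speaks of a stay. This stands: the ward-day bias follows from one reading, and it is not an established feature of the plan. It does not rescue the method, which fails under readings B and C for a different reason.

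A second reply is that rules for ICU days belong in a statistical analysis plan. That is fair for start and stop rules and for the score of never-admitted patients. But the protocol does not leave the method open: it names one, and that method does not suit the endpoint.

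Third, the absence of ICU dates from Table 3 does not show that they go uncollected. The case report form is not shown, Section 4.5.3.2 has an item recorded when ICU is needed, and Section 7.3 makes the hospital chart the source. This also stands.

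Finally, the endpoint is secondary and descriptive. That limits the importance of the point but does not remove it.

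**Conclusion.** The prescribed analysis does not fit ICU stay on any of the three readings. On the most natural one it measures time to ICU exit, with one extra day for each day of delayed entry. On the other two that bias disappears, but patients never admitted have no event time or the comparison falls to a subgroup formed after randomisation.

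A reader might infer three stronger things that the protocol does not support:
- **That ward days will certainly be counted as ICU days.** The wording permits this but does not state it.
- **That a two-day harm is to be expected.** The 11 versus 13 days only restates the assumed entry times.
- **That preventing ICU admission would earn no credit.** This depends on whether never-admitted patients are scored zero, in which case prevention is credited, or left out. The protocol says neither.

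The range of 18 to 54 patients with an ICU time rests on assumed ICU rates. The correction is worth making because ICU use is central to the stated purpose and the change is small. The primary analysis is not affected.

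**What to change.** In Section 6.3.3.2, under Time in ICU department and in hospital, keep the randomisation-based time-to-event analysis for time to hospital discharge only. For ICU use, analyse days alive and out of ICU from randomisation to Day 28 in all randomised patients, give deaths by Day 28 the worst value, and compare the arms by a rank test. Report ICU days descriptively beside it.

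Two simpler repairs are less good. Starting the clock at ICU admission limits the comparison to admitted patients. Comparing ICU days with zero for those never admitted ranks an early death on the ward as the best possible outcome.

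Record ICU admission and discharge dates from the hospital chart. Because the Day 28 contact has a window (2 days either way in Table 3, 5 days in Section 4.5.1.6), the count should run to Day 28 from the chart and not to the date of contact.

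The cost is a reworded paragraph, two dates per admission and the loss of a hazard ratio for ICU time.

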##### 3.2.1 Secondary endpoints supporting the secondary objective

- Total mortality rate (day 28)
- Mortality 48 hours, 7 days, in ICU and hospital
- Viral clearance / viral shedding
- Frequency and severity of AEs:
  - Treatment-emergent severe fatal and life-threatening serious adverse events (SAEs).
  - Adverse events leading to premature discontinuation of study treatment.
  - Anaphylactic/anaphylactoid reactions.

- 
- Anakinra treatment group: Severe neutropenia.
  - Treatment-emergent laboratory abnormalities.

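### Time in ICU and in hospital is sent to Kaplan-Meier, log-rank and Cox without defining the event or naming death as a competing event, so a drug that lowers mortality can show no effect or a longer stay.

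*Protocol*

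**What the plan says.** Section 3.1.2 lists stay in ICU and in hospital, in days, among the secondary endpoints supporting the primary objective. The analysis is in Section 6.3.3.2, under the heading for time in ICU and in hospital: "Time in ICU and time in hospital (from the point of randomization) will be analyzed at the end of the follow-up period". The next sentence gives the method: "This endpoint will be analyzed as for time to mechanical ventilation".

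The method referred to stands earlier in the same section: "plotting Kaplan-Meier curves for each of the 2 treatment groups and by pairwise comparisons (anakinra versus standard of care) using the log rank test". The effect measure follows: "Hazard ratios will be estimated using the Cox proportional hazards model and these will be presented together with 90% two-sided confidence intervals".

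Neither paragraph states which event ends a stay, or what happens to a patient who dies before discharge. Section 6.3.8 says only that missing data will not be computed. Deaths before discharge are plainly expected, since Section 3.2.1 lists as an endpoint "Mortality 48 hours, 7 days, in ICU and hospital". Section 6.3.1 makes the secondary endpoints descriptive and any p-values exploratory.

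**The concern.** For time to mechanical ventilation, a later event is the better result. For length of stay, an earlier end is better, but only if the patient leaves alive. A stay can end by live discharge or by death, and a single-event survival analysis does not separate the two unless the plan says how.

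There are two usual ways to force the data into the stated method:

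- **Deaths censored.** The Kaplan-Meier estimator treats the dead as patients who would later go home at the same rate as those still in hospital, so 1 minus Kaplan-Meier overstates live discharge.
- **Death counted as the end of stay.** An early death becomes a short stay, and a drug that keeps patients alive appears to lengthen stay.

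ICU time raises a second difficulty. Section 4.3.2 excludes patients who need intubation or invasive ventilation at the start, so many ICU stays will begin after randomization and some patients will have none. A duration counted from randomization does not measure time in ICU for either group.

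Sections 2.1 and 2.2 give preserving access to intensive care as the trial's purpose. These endpoints bear directly on that purpose, so a misleading result here would matter to readers even though it is not the primary one.

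**Working it through.** The protocol gives no event rate, effect size or power for these endpoints, so there is no planned figure to reproduce. Two checks were made. All hazards, mortality effects and lengths of stay below are assumptions. The lowest control mortality, 3.7%, is the lethality quoted in Section 2.1. The highest pair, 64.7% against 34.6% deaths, comes from the survival figures for the sepsis trial quoted in Section 2.1 (100 − 35.3 and 100 − 65.4).

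**1. Closed form, constant daily hazards.** Let d be the hazard of live discharge, m the hazard of death, and t = 28 days.

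- True live discharge: d/(d+m) × [1 − exp(−(d+m)t)]
- 1 minus Kaplan-Meier, deaths censored: 1 − exp(−dt)
- 1 minus Kaplan-Meier, death as event: 1 − exp(−(d+m)t)

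Take d = 0.08 and m = 0.01. Then exp(−2.24) = 0.106 and exp(−2.52) = 0.080. True live discharge is 0.889 × 0.920 = 81.7%, the censored curve gives 89.4%, and death as event gives 92.0%. Suppose the drug halves m and leaves d unchanged. The same formulas, with lower and higher m added to show a range, give (control → anakinra):

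| m | True live discharge | Deaths censored | Death as event |
|---|---|---|---|
| 0.0035 → 0.00175 | 86.6% → 87.9% | 89.4% → 89.4% | 90.3% → 89.9% |
| 0.01 → 0.005 | 81.7% → 85.4% | 89.4% → 89.4% | 92.0% → 90.7% |
| 0.02 → 0.01 | 75.1% → 81.7% | 89.4% → 89.4% | 93.9% → 92.0% |

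These values of m correspond to control mortality by Day 28 of about 3.8%, 10.2% and 18.8%, from m/(d+m) × [1 − exp(−(d+m)t)]. The null result with deaths censored is built in, because d is held equal in the two arms.

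**2. Simulation.** This used 90 patients per arm (Section 6.1), 28 days of follow-up and 500 replicates, with 20,000 per arm for the large-sample hazard ratio. The drug halves mortality (or moves it from 64.7% to 34.6%) and does not change the stay of patients who would survive in either arm. Assumed means are about 11 days for ordinary survivors' stay and for time to death, and about 12, 19 or 25 days for the stay of patients the drug saves. A hazard ratio above 1 means earlier discharge; each range runs over the three assumed stays.

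| Control mortality | Death as event | Deaths censored | Dead kept undischarged to Day 28 |
|---|---|---|---|
| 3.7% | 0.97–1.01 | 0.99–1.03 | 1.04–1.07 |
| 20% | 0.82–0.98 | 0.92–1.11 | 1.14–1.26 |
| 30% | 0.75–0.97 | 0.89–1.19 | 1.18–1.43 |
| 64.7% (vs 34.6%) | 0.59–0.95 | 1.01–1.79 | 1.70–2.32 |

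At 20% against 10% deaths, with saved patients staying about 25 days:

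- With death as event, 91% of simulated trials give a hazard ratio below 1, and 23% are significantly worse for anakinra at two-sided 5%.
- With deaths censored, Kaplan-Meier puts discharge by Day 28 at 96.7% on control and 93.8% on anakinra. The true live-discharge proportions are 78.9% and 85.9%, so the direction is reversed.

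Keeping the dead undischarged to Day 28, which with complete follow-up is the cumulative-incidence approach, favoured the life-saving drug in all 18 scenarios run.

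**The case against.** The strongest reply is that the protocol fixes neither harmful treatment of death. The analyst could keep the dead in the risk set as undischarged until Day 28. With complete follow-up, the stated Kaplan-Meier and log-rank methods then describe live discharge correctly. On that view only a rule for death is missing, and such rules are often left to the statistical analysis plan, which is not available here. This stands in part. A reader might infer that the method is wrong however it is applied, and the text does not support that. But the protocol does name the method, borrows it from an endpoint of a different kind, and leaves open the two usual treatments that mislead.

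A Cox model with deaths censored also estimates a legitimate cause-specific hazard of discharge, so censoring is not an error in itself. The error would be to read that hazard ratio, or 1 minus Kaplan-Meier, as the effect on length of stay.

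The size is uncertain. Near 3.7% mortality the distortion is small. If saved patients leave as quickly as others, the censored analysis still leans the right way (1.03 to 1.19 for control mortality of 3.7% to 30%). The drug may also speed recovery, which both checks assume it does not.

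Two further inferences should be resisted. Section 6.3.3.2 does not restrict ICU time to patients admitted to ICU, so a comparison within a group formed after randomization cannot be attributed to the plan. And because mortality is analysed separately, a reader would see a survival difference beside the stay result.

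**Conclusion.** The point holds as a weakness in a secondary analysis that should be corrected. The protocol assigns a single-event survival method to ICU and hospital stay, without an event definition and without treating death as a competing event. Under the two usual treatments of death, a drug that lowers mortality can appear to have no effect or to lengthen stay. With death as the event, the simulated hazard ratio runs from negligible at 3.7% control mortality to clearly unfavourable at 20% and above when saved patients stay long. With deaths censored, the sign depends on how soon saved patients go home. All sizes rest on assumed mortality and stays; the protocol gives no expected mortality for this trial.

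ICU time is separately ill-defined for patients who enter ICU after randomization or never. No size was computed for that part.

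A reader might infer that the trial's main conclusion is at risk. It is not: the endpoint is secondary and descriptive, and the primary analysis does not use it.

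**What to change.** In Section 6.3.3.2, replace the cross-reference for time in ICU and in hospital with two explicit analyses, both by randomised arm:

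- **Hospital stay:** cumulative incidence of live discharge from randomization to Day 28, with death as a competing event. Show Aalen-Johansen curves and compare the arms by Gray's test or, equivalently with complete follow-up, by keeping the dead undischarged to Day 28. If a cause-specific hazard ratio is also reported, label it as such and not as the effect on length of stay.
- **ICU use:** ICU-free days alive to Day 28 in all analysed patients, with death scored 0, compared by a rank test. Patients never admitted to ICU and those admitted late are then both defined.

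For hospital stay the cost is wording only, since Section 4.5.3.7 and the schedule of events already collect survival and hospital discharge. The ICU analysis also needs ICU admission and discharge dates. The schedule and the efficacy assessments do not list them (ICU appears there only in connection with the MEWS score), so their capture in the CRF should be confirmed. The ICU stay endpoint in Section 3.1.2 needs those dates in any case.
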